### 2.6. Adherence

Participants in the intervention group will be asked to complete activities at the end of each psychological content module and will be invited to put into practice what they had learned during the week. To increase the women’s motivation and improve adherence, while using the Healthy Moms and Babies app, women will be randomly asked true/false quiz questions about the content that is already covered in the modules. There is no compensation to participate in the study.

### 2.7. Ethical Standards

This study is conducted according to the principles expressed in the Declaration of Helsinki. This study has been approved by the Institutional Review Board at the San Carlos Clinic Hospital (Reference number 19/184-E). Handling of the study data complies with all the Spanish required standards for data protection. Electronic informed consent will be obtained from all the participants, and the confidentiality of all the provided information will be ensured.

### 2.8. Sample Size

A representative sample size was calculated according to the number of newborns in the previous year in each country. Thus, we estimated a minimum sample size of 385 participants, based on an α-level of 0.05 and heterogeneity equal to 50%.

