In the field of e-health, mobile applications represent a tool with great potential in the gestational and postpartum periods. A study by Osma et al. [37] concluded that pregnant women use the internet more frequently from their smartphones than from their computers, with the mobile phone being the digital device that is most used by this population. Most women use pregnancy and parenting-related applications [38,39], and even women with few economic resources make use of these applications [40]. Pregnant women use applications for information when conventional antenatal care resources do not meet their needs or when they experience difficulty accessing these resources [41]. In addition, these applications allow for screening, assessment, and psychological interventions to be performed anywhere, anytime and at a low cost [42], increasing the chances of early detection and of providing rapid and appropriate interventions [43]. A meta-analysis of mobile application interventions for mental health confirmed their efficacy, highlighting their potential as cost-effective and accessible interventions for women who are unable to receive standard psychological treatment [44], and showed that these interventions offer promising results in improving and maintaining health. Notably, most of the research on perinatal depression prevention with e-health has been carried out in English-speaking countries [45] (e.g., the United States and Australia), while studies in Spanish are limited to Barrera and her colleagues. During 2019 [46], Spain reported 377,906 single births, 8134 double births, and 93 triple births or more; therefore, the number of women suffering from postpartum depression could range from 42,643 to 104,782. An application designed in the Spanish language will be very helpful to address the needs of the many women who could suffer depression all over the country.

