The primary objective of the current study is to determine whether a Spanish preventive psychological intervention app designed in Spain, Healthy Moms and Babies, is superior to the general delivery of pregnancy information (breastfeeding advice, nutrition and exercise, birth facts, fetal development information and answers to frequently asked questions) in the prevention of postpartum depressive symptomatology. The secondary objective is to examine whether this same intervention is more effective than the general delivery of information about pregnancy in preventing postpartum anxious symptomatology.

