## 2. Methods

### 2.1. Design and Population

The design is a two-armed randomized controlled study, with patients assigned to the intervention group, who will have access to the psychological content of the Healthy Moms and Babies app and general information about pregnancy, while those assigned to the control group, who will only have access to the informational content provided by the e-health tool. Participants will be assessed before and after using the app and at three and six months after their due date. Figure 1 shows a flow chart of the study design. Recruitment will take place between 2020 and 2022.

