### 2.3. Outcomes and the Allocation of Participants to Trial Groups

#### 2.3.1. Primary Outcome

The primary outcome measure will be the difference in the mean scores between the intervention and control groups on the Patient Health Questionnaire-9 (PHQ-9) at the end of the psychological modules of the Healthy Moms and Babies application (in the case of the control group, the post assessment will be done six weeks after starting the PPP for the first time) and at three and six months after the delivery date.

The PHQ-9 is a nine-item instrument that assesses the severity of depressive symptomatology according to the following criteria of the Diagnostic and Statistical Manual of Mental Disorders [47]: depressed mood, markedly diminished interest in usual activities, significant increase or loss of appetite/weight, insomnia/hypersomnia, psychomotor agitation/retardation, fatigue or loss of energy, feelings of worthlessness or guilt, difficulty with thinking, concentrating or making decisions, and recurrent thoughts of death or suicide. The items are rated on four-point Likert-type scales, ranging from 0 (never) to 3 (almost every day), with higher scores indicating high severity of depressive symptoms (range 0–27). A score of 10 is the cut-off point recommended in clinical practice for estimating the presence of depressive symptoms [48,49]. However, considering that our aim is to prevent depressive symptoms, we will include all pregnant women who obtain a score equal to or greater than 5. The PHQ-9 has been validated in Spanish-speaking samples and in Spanish pregnant women [50].

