### 2.9. Analysis Plan

The primary analysis will compare the mean score on the PHQ-9 between the two trial groups before and after the intervention and at three and six months postpartum to assess the effectiveness of the Healthy Moms and Babies app in preventing postpartum depressive symptomatology. Similar analyses will be conducted for the secondary outcome on anxious symptomatology. In addition, a qualitative study of the participants’ responses to the developmental exercises proposed in some modules will be conducted. The severity of depressive and anxious symptomatology will be studied in relation to the sociodemographic characteristics that were assessed, and the participants’ use of the application will be examined (number of visits to the app, most visited content, time invested in completing the modules, the results of the quiz questions, etc.).

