## 4. Discussion

Perinatal depression can threaten the physical and psychological health of the mother, put the baby’s development at risk, and affect the creation of the bond between mother and baby, the couple’s relationship, and the family [16]. To avoid these negative consequences, health providers [34] and institutions [19] must stress the need to implement preventive interventions for perinatal depression. Pregnancy is a favorable time to address prevention [3,24]. However, help-seeking rates during this period are low due to multiple barriers and difficulties, including the lack of information, costs of access to conventional treatments, and fear of stigmatization and public exposure to peers [33,34].

E-health interventions, including mobile applications, offer advantages in overcoming the barriers described above, facilitating access to interventions at low costs and in a simple way. Moreover, these applications can reach women all over the world, including those women who experience difficulty traveling to receive health services [57,58]. Digital tools offer new and tailored content, allowing women to access the tools at their own pace and preserving their anonymity [59].

However, despite the many virtues of online interventions [60], they also have some limitations. Participation and retention can be difficult to sustain in an online intervention, leading to high drop-out rates and low adherence [29]. It is therefore, important to consider the additional moderation of the intervention by a professional, analyze women’s use of the tool, and adapt the application to their needs as much as possible [61].

Mental health applications are not intended to replace professional clinical services. Instead, these apps can be a cost-effective, easily accessible, low-intensity resource for women who are unable to receive standard psychological treatment, or a good complementary resource to face-to-face counseling. The Healthy Moms and Babies app was developed by a multidisciplinary team that aims to contribute to increasing the scientific evidence on the effectiveness of CBT-based mobile applications to prevent postpartum depression.

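### The sample size of 385 rests on a survey-precision argument for one proportion, which does not apply to the two-arm comparison of mean PHQ-9

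*Protocol article*

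**What the plan says.** Section 2.8 is two sentences long. The first gives the basis: "A representative sample size was calculated according to the number of newborns in the previous year in each country". The second gives the inputs and the result: "we estimated a minimum sample size of 385 participants, based on an α-level of 0.05 and heterogeneity equal to 50" per cent. It names no arms, power, PHQ-9 standard deviation or target difference.

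The rest of the article describes a different kind of question. Section 2.1: "The design is a two-armed randomized controlled study". The objective at the end of the Introduction is to learn whether the app "is superior to the general delivery of pregnancy information". Section 2.3.1: "The primary outcome measure will be the difference in the mean scores between the intervention and control groups on the Patient Health Questionnaire-9 (PHQ-9"), after the intervention and at three and six months after delivery. Section 2.9: "The primary analysis will compare the mean score on the PHQ-9 between the two trial groups before and after the intervention" and at the two later follow-ups. No section connects 385 to that comparison.

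**The concern.** A sample size for a superiority trial should follow from the comparison to be made: how large a difference, against what variability, with what power. Section 2.8 starts instead from representativeness of a birth population and a 50% heterogeneity term. Those are the ingredients of a prevalence survey. They have no place in a calculation for a difference between two means.

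This goes beyond a detail left to a fuller protocol or an analysis plan. The article gives a rationale, with inputs and a result, and that rationale does not fit its own primary outcome. No later document can make a one-proportion precision formula bear on a difference in mean PHQ-9. At stake is the only quantitative justification offered for the size of the trial: as written, a reader cannot tell what PHQ-9 difference it was built to detect.

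**Working it through.** **Inputs from the article.** N = 385 as a minimum, alpha 0.05, heterogeneity 50% read as p = 0.5 (section 2.8). Section 2.8 does not give the birth count it used. The only one in the article is in the Introduction: "Spain reported 377,906 single births, 8134 double births, and 93 triple births or more".

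**Inputs that are assumptions.** A ±5-point margin of error, two-sided testing, 1:1 allocation, PHQ-9 SD of 3 to 6 points, losses of 30% and 50%. The article states none of these.

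**Step 1: reproduce 385.** The precision formula for one proportion is n = z² p(1 − p) / e².

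- z = 1.96, p = 0.5, e = 0.05: 1.96² × 0.25 / 0.0025 = 384.15, rounded up to 385. This matches exactly.
- Margins of 3, 4 and 6 points give 1068, 601 and 267. A one-sided alpha with e = 0.05 gives 271. None matches.
- Finite-population correction, n / (1 + (n − 1)/N), with N = 377,906 + 8,134 + 93 = 386,133: 383.77, rounded up to 384. With single births only (377,906) it is 383.76, also 384.

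The match is therefore to the uncorrected formula, and the birth count makes almost no difference to the answer.

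**Step 2: try the formula the trial needs.** For two means with equal arms, n per arm = 2 (z₀.₉₇₅ + z_power)² / d², where d is the between-arm difference divided by the SD. It cannot be run from section 2.8, because the difference, the SD and the power are all absent. A total near 385 does come out for d of about 0.285 to 0.29 at 80% power, or 0.33 at 90%. But the section states no such d, and a heterogeneity of 50% has no role in this formula.

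**Step 3: what 385 randomised women would detect.** Invert the formula: d = (z₀.₉₇₅ + z_power) × √(2 / n per arm), for one unadjusted comparison at one time point, with n per arm = 192.5 before losses.

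| Women analysed | Power | d | PHQ-9 points, SD 3 to 6 |
|---|---|---|---|
| 385 (no loss) | 80% | 0.286 | 0.86 to 1.71 |
| 385 (no loss) | 90% | 0.330 | 0.99 to 1.98 |
| about 270 (30% loss) | 80% | 0.341 | 1.02 to 2.05 |
| about 193 (50% loss) | 80% | 0.404 | 1.21 to 2.42 |

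The first row in full: (1.960 + 0.842) × √(2 / 192.5) = 2.802 × 0.1019 = 0.286. With all 385 analysed, power is about 50% for d = 0.2 and about 84% for d = 0.3. Adjusting for baseline PHQ-9 would lower every d in the table.

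**The case against.** The best reply is that the number may be perfectly serviceable. With full follow-up 385 detects a standardised difference of about 0.29, and section 2.8 calls it a minimum. That stands: a wrong derivation does not make the number wrong, and the documents give no target difference against which to call it too small. It is also fair that an article may leave power, SD and attrition to a fuller document. Their absence alone would not be a finding; the stated survey rationale is. The ±5-point margin is inferred, but the conclusion does not hang on it, since the section's own terms already place the calculation outside a comparison of means.

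A reader might be tempted to go further in four ways that the documents do not support.

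- **A null result would be uninterpretable.** It would not. It can be read from the confidence interval for the mean difference, set against a worthwhile difference, whatever formula produced N.
- **The plan forecasts heavy attrition and ignores it.** The Discussion says "Participation and retention can be difficult to sustain in an online intervention, leading to high drop-out rates and low adherence", but as a cited limitation of online interventions in general. It gives no rate for this trial, and the article describes adherence measures and email reminders. The loss rates above are illustrations only.
- **385 counts women before PHQ-9 screening, so far fewer are randomised.** Section 2.5 includes only women scoring 5 to 19, so the natural reading of a study minimum is women included. Because the same section also calls the excluded women participants, the unit is worth stating. No in-range rate is given from which to compute a shortfall.
- **The reference to each country must be an error because the trial is confined to Spain.** Eligibility in section 2.4 requires fluent Spanish, not residence in Spain, and recruitment also runs on social media. The phrase is unclear, but it is not shown to be wrong on that ground.

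**Conclusion.** The point holds in a limited form. The stated basis for 385 is the precision size for one proportion, reproduced exactly at 95% confidence and an inferred ±5 points, and it has no bearing on a two-arm superiority comparison of mean PHQ-9. As justified, the figure carries no power and no detectable difference for that comparison.

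The size of the matter is what section 2.8 leaves unsaid: a detectable d of about 0.29 (80% power) or 0.33 (90%) with everyone followed up, moving to about 0.34 or 0.40 at 80% power if 30% or 50% were lost. These values assume 1:1 randomisation of all 385, two-sided alpha 0.05 and an unadjusted t-test. Whether they are good enough depends on a worthwhile difference that the article does not state, so inadequacy of 385 is not established.

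**What to change.** Rewrite section 2.8:

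1. Delete the representativeness, newborn and heterogeneity rationale.
2. State that 385 counts women randomised, that is, those with a baseline PHQ-9 of 5 to 19.
3. Present the size as a two-arm comparison of means with two-sided alpha 0.05, the allocation ratio and an assumed PHQ-9 SD with its source.
4. State the PHQ-9 difference considered worthwhile. Beside it, give the difference detectable at 80% and 90% power, for 385 and for 385 less an assumed attrition. Say whether baseline adjustment is counted on.

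The cost is one paragraph. Correcting the rationale does not by itself require more enrolment, but it does not certify 385 as adequate either; that depends on how the detectable difference compares with the worthwhile one. The downside is presentational: the detectable difference after attrition will look less favourable than a bare figure of 385.

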### 2.9. Analysis Plan

The primary analysis will compare the mean score on the PHQ-9 between the two trial groups before and after the intervention and at three and six months postpartum to assess the effectiveness of the Healthy Moms and Babies app in preventing postpartum depressive symptomatology. Similar analyses will be conducted for the secondary outcome on anxious symptomatology. In addition, a qualitative study of the participants’ responses to the developmental exercises proposed in some modules will be conducted. The severity of depressive and anxious symptomatology will be studied in relation to the sociodemographic characteristics that were assessed, and the participants’ use of the application will be examined (number of visits to the app, most visited content, time invested in completing the modules, the results of the quiz questions, etc.).

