### 2.2. Recruitment of Women

#### 2.2.1. Identification and Recruitment in the Obstetrics and Gynecology Department

The obstetricians and midwives who collaborate in the research will invite pregnant women who are undergoing obstetric follow-up at the Hospital Clínico San Carlos in Madrid to participate in the study. Interested individuals will be given a leaflet explaining the research with a QR code that they can scan with their smartphone to visit the initial web form that collects contact and socio-demographic data (age, gestational week, place of origin and residence, reference hospital, completed studies, employment status, marital status, and number of pregnancies, cesarean sections and/or previous abortions).

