### 2.4. Inclusion and Exclusion Criteria

Inclusion criteria include being pregnant (participants can join the study at any time during their pregnancy), being over 18 years of age, understanding and speaking Spanish fluently, having a smartphone and the basic skills to operate it, and giving consent to participate in the study. The exclusion criteria for the study are not being pregnant, not understanding or speaking Spanish fluently and not having a smartphone or the basic skills to use it.

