### 2.5. Randomization

When participants access the Healthy Moms and Babies application for the first time, they will complete the baseline assessment including the PHQ-9 and GAD-7. Only participants who score between 5 and 19 on the PHQ-9 will be included and randomized into the treatment and control groups.

Based on the PHQ-9 score, called the $value, the Plesk software will distribute participants according to their level of symptomatology. Participants scoring <5 on the PHQ-9 have minimal depressive symptoms and therefore they will be excluded from the study and no further evaluation will be performed, but they will be offered access to the pregnancy information content. Participants scoring >19 on the PHQ-9 are considered to have severe symptomatology and will also be excluded from the study. In this case, these participants will be blocked from accessing the Healthy Moms and Babies application because it was not designed to address severe depressive symptomatology. Women will receive an alert message telling them to share their distress with someone close to them and to see a specialist for appropriate psychological care. Eligible patients (PHQ-9 score between 5 and 19) will be randomly assigned to the intervention and control groups according to the standard PHP function (mt_rand()) automatically generated by a computer. Women in the intervention group will have access to the psychological content modules and the general pregnancy information on the Healthy Moms and Babies app; women in the control group will only be able to access the informational content.

An independent researcher will program the mathematical algorithm that performs the randomization. Subsequently, simple blinding will be used, and participants will not be informed of the group to which they are assigned. The allocation will be known to the study team after it is performed automatically.

Outcome measures will be assessed at baseline, immediately after the intervention, and three and six months after the delivery date. At follow-up, questionnaires will be sent at the appropriate time by email and will be completed by the women via a web form.

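### The primary analysis lists baseline PHQ-9 as a comparison occasion and does not say it will be a covariate; a baseline-adjusted comparison would be at least as precise at almost no cost

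*Protocol article*

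**What the plan says.** Section 2.9 (Analysis Plan) defines the primary analysis: "The primary analysis will compare the mean score on the PHQ-9 between the two trial groups before and after the intervention". The sentence continues with the three- and six-month postpartum assessments, and the GAD-7 is to be handled in a similar way. No model, covariate or change score is named.

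Section 2.3.1 defines the primary outcome as the difference between arms in mean PHQ-9 at three occasions: the end of the psychological modules (six weeks after starting, for controls), and three and six months after delivery. The abstract gives the same three. Baseline is not among them.

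Section 2.5 says that at first access to the app, before allocation, "they will complete the baseline assessment including the PHQ-9 and GAD-7". The baseline score also decides entry: "Only participants who score between 5 and 19 on the PHQ-9 will be included and randomized into the treatment and control groups". The assessment schedule there is: "Outcome measures will be assessed at baseline, immediately after the intervention, and three and six months after the delivery date". Allocation uses a computer random-number function, and no stratification is described. Gestational week is recorded on the initial web form (section 2.2.1), and under section 2.4 "participants can join the study at any time during their pregnancy".

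**The concern.** Two things in section 2.9 do not sit well.

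First, it places the pre-intervention score in the same list as the outcome occasions, so it does not match the outcome definition in section 2.3.1. In a randomised trial, a between-group comparison at baseline reflects only chance. It cannot inform the effectiveness question that section 2.9 says the analysis serves.

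Second, it does not say that baseline PHQ-9 will be used to sharpen the post-baseline comparison, although the score is available for every randomised woman. At stake is precision: wider confidence intervals and lower power than the same data can give. This matters more here because the sample size was not derived from a two-arm power calculation, and because the Discussion itself warns of high drop-out in online interventions.

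**Working it through.** **The plan's own figure.** Section 2.8 gives a minimum of 385, "based on an α-level of 0.05 and heterogeneity equal to 50" per cent. The single-proportion precision formula n = z² p(1 − p) / e², with z = 1.96, p = 0.50 and an assumed margin e = 0.05 (not stated), gives 384.15, rounded up to 385. The figure therefore reproduces as a survey size. It contains no effect size, SD, power or correlation for the PHQ-9 comparison.

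**Inputs for the check.** From the documents: 385 women and α = 0.05. Assumed: two-sided testing, 1:1 allocation (192.5 per arm), no loss, 80% power, and a baseline-to-follow-up correlation r of 0.2 to 0.5.

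**Step 1: which readings are possible, and how precise is each?** Write s0 and s1 for the baseline and follow-up SDs. The variance of the between-arm estimate is proportional to:

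- separate comparisons of follow-up means: s1²
- change scores: s1² + s0² − 2r·s0·s1, which is 2(1 − r)·s1² if the SDs are equal
- group-by-time with baseline as an ordinary outcome: the contrast from baseline to a visit is the change-score contrast, unless the baseline means are constrained to be equal, which is not stated
- baseline as covariate: (1 − r²)·s1²

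Follow-up means minus covariate adjustment leaves r²·s1². Change scores minus covariate adjustment leaves (s0 − r·s1)². Neither can be negative, so in large samples adjustment is never less precise than either alternative, whatever r and whatever the SDs.

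**Step 2: detectable difference.** Unadjusted: (1.960 + 0.842) × √(2 / 192.5) = 2.802 × 0.1019 = 0.286 SD. Adjusted: 0.286 × √(1 − r²). Equivalent unadjusted sample: 385 / (1 − r²). Power is at an illustrative true difference of 0.25 SD, where the unadjusted value is 68.9%. The change-score column assumes equal SDs.

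| r | Variance factor, adjusted | Variance factor, change score | Detectable difference (SD) | Equivalent N | Power, adjusted |
|---|---|---|---|---|---|
| 0.2 | 0.96 | 1.6 | 0.280 | 401 | 70.7% |
| 0.3 | 0.91 | 1.4 | 0.272 | 423 | 72.9% |
| 0.4 | 0.84 | 1.2 | 0.262 | 458 | 76.3% |
| 0.5 | 0.75 | 1.0 | 0.247 | 513 | 80.8% |

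With equal SDs and r below 0.5, change scores are less precise than ignoring baseline altogether.

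**Step 3: loss to follow-up.** With 30% loss (assumed), the unadjusted detectable difference is 0.341 SD, against 0.326 SD at r = 0.3 and 0.296 SD at r = 0.5. The proportional gain is unchanged.

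**Step 4: chance imbalance.** With 192.5 per arm, baseline means differ by chance within about ±1.96 × 0.1019 = ±0.20 SD (95%). An unadjusted follow-up comparison carries r times that: about 0.04 SD at r = 0.2 and 0.10 SD at r = 0.5.

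**The case against.** The strongest reply is that this is a condensed article, and that the model and covariates are commonly left to a full protocol or analysis plan, neither of which is shown. ANCOVA and mixed models also compare group means, so the sentence does not exclude adjustment. That stands. A reader might infer that the trial has chosen raw means in place of adjustment; the article says neither that scores will be unadjusted nor that covariates are ruled out.

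Three other stronger readings also go too far:

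- **A planned baseline significance test.** The text speaks of comparing, not testing, and section 2.3.1 keeps baseline out of the outcome.
- **Bias from chance imbalance.** Under randomisation the unadjusted estimate is unbiased, its confidence interval already covers chance imbalance, and only r times the imbalance enters.
- **A large gain.** At r = 0.6 the gain would be worth 602 unadjusted women, but no correlation is documented. The entry range of 5 to 19 tends to lower it, and the long, variable gap from any point in pregnancy to six months postpartum may lower it further.

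Nor do the documents show that gestational week predicts PHQ-9.

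It can also be said that the wording fits a repeated-measures or change analysis that does use baseline. That is a fair reading, but it does not dispose of the point: with baseline as an unconstrained outcome, such analyses are still no more precise than adjustment. The mismatch between sections 2.9 and 2.3.1 also remains, because it is in what the article states, not in what it omits.

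**Conclusion.** The point holds as one of efficiency and clarity. Section 2.9 lists an occasion that is not part of the primary outcome, and nowhere does the article say that baseline PHQ-9 will be a covariate. None of the natural readings is more precise in large samples than a baseline-adjusted comparison.

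The size rests on the assumed r, 1:1 allocation and 385 analysed without loss. Against follow-up means, the variance falls by 4 to 25% for r of 0.2 to 0.5, and the detectable difference falls from 0.286 SD to between 0.280 and 0.247 SD. The lower part of that range is more likely: for r of 0.2 to 0.4 the variance gain is 4 to 16%. The validity of the trial is not in question. This is a modest improvement worth making because it is nearly free, and confidence is moderate because a fuller plan may already contain it.

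**What to change.** Restate section 2.9 so that the primary comparison covers only the post-baseline PHQ-9 scores, by randomised arm, with baseline PHQ-9 as a covariate. Either ANCOVA at each time point or a mixed model with arm-by-time terms would serve. Report baseline scores descriptively by arm, without a between-group test. Treat GAD-7 in the same way, with baseline GAD-7 as the covariate. Gestational week at entry is an optional further covariate.

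If the statistical analysis plan already specifies this, align the public wording with it. The cost is a change of wording: all of these variables are already collected, and neither the visits nor the sample size need change.

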## Abstract

Depression is the most common psychological disorder during the perinatal period, and its negative effects extend to mothers, babies, their family and society. Scientific evidence points to the urgency of designing preventive interventions and concludes that the gestational period is the most appropriate time to implement these interventions. However, many pregnant women do not seek professional help due to a lack of knowledge about the importance of mental health, its impact, and the available intervention options, as well as a lack of time and financial resources. E-health interventions can be an efficient, cost-effective, and accessible resource for preventing postpartum depression that can circumvent the barriers that pregnant women face. This randomized clinical trial will examine the efficacy of Healthy Moms and Babies, an app aimed at preventing postpartum depressive symptomatology. The second objective of this study is to analyze the effectiveness of the tool in preventing anxious symptomatology. The primary outcome measure is the difference in the mean score between the intervention and control groups on the Patient Health Questionnaire-9 (PHQ-9) at the end of the intervention and at 3 and 6 months postpartum. The secondary outcome will be determined by using the Generalized Anxiety Disorder Screener (GAD-7) at the same time points. The research findings can be used to determine pregnant women’s use of the e-health application for the prevention of postpartum depression, whether the Healthy Moms and Babies intervention app is an effective and useful resource, and what modifications will need to be made to the tool in future updates.

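### The primary outcome is fixed at three unranked PHQ-9 times, one of which can fall before birth although the objective is postpartum symptoms

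*Protocol article*

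**What the plan says.** Section 2.3.1 of the protocol article defines the outcome: "The primary outcome measure will be the difference in the mean scores between the intervention and control groups" on the PHQ-9. The first time is "at the end of the psychological modules of the Healthy Moms and Babies application"; for the control arm, "the post assessment will be done six weeks after starting the PPP for the first time". The definition then continues "and at three and six months after the delivery date". The Abstract gives the same list: "at the end of the intervention and at 3 and 6 months postpartum". Section 2.9 describes one primary analysis, which will "compare the mean score on the PHQ-9 between the two trial groups before and after the intervention and at three and six months postpartum", and gives its purpose as judging how well the app works "in preventing postpartum depressive symptomatology".

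The objective at the end of section 1 is superiority over general pregnancy information "in the prevention of postpartum depressive symptomatology". Section 3.2 also places the goal in the postpartum period.

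Three other statements matter. Section 2.4 lets women join at any stage of pregnancy. Section 3.3 describes eleven modules, one released every four days, with an average duration of six weeks. Section 2.8 contains the only significance level, 0.05, and ties it to no time point.

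**The concern.** Two problems follow from the definition in section 2.3.1.

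First, the outcome and the objective do not match. The objective concerns symptoms after birth. One of the three primary scores can be taken before birth, yet it has the same standing as the two postpartum scores. A short-lived difference in late pregnancy would meet the primary outcome as defined while saying nothing about postpartum symptoms.

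Second, the document does not say what counts as success. With three unranked times and no rule for combining them, whoever reads the results can choose the favourable time. Section 2.5 adds that the study team knows the allocation once it has been made, so the choice is best fixed before any comparison by arm.

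**Working it through.** **1. The plan's own figure.** Section 2.8 gives 385 from a level of 0.05 and heterogeneity of 50%. The formula for estimating one proportion, with an assumed margin of 5 percentage points (not stated), gives n = 1.96² × 0.5 × 0.5 / 0.05² = 384.15, rounded up to 385. The figure is reproduced. It does not size a two-arm comparison, so it cannot show which time point the trial was designed to test.

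**2. When the first primary score falls.** Eleven modules at four-day spacing take 10 × 4 = 40 to 11 × 4 = 44 days, or 5.7 to 6.3 weeks. This agrees with the stated six weeks. With an assumed term of 40 weeks, the score precedes birth for a start before week 40 − 6 = 34. If entry is spread evenly from week L to week 40 (an assumption), the antenatal share is (34 − L)/(40 − L):

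| Entry window | Calculation | Antenatal share |
|---|---|---|
| Week 8 to 40 | 26/32 | 81% |
| Week 12 to 40 | 22/28 | 79% |
| Week 20 to 40 | 14/20 | 70% |
| Week 28 to 40 | 6/12 | 50% |

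**3. False-positive risk under one possible reading.** Suppose each of the three times is tested at two-sided 5% and any one significant result counts as success. If the tests are independent, the risk is 1 − 0.95³ = 14.3%. For correlated tests, 2 million draws of three equally correlated normal statistics, with success when any |Z| exceeds 1.96, give:

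| Assumed correlation | Risk that at least one is significant |
|---|---|
| 0 | 14.3% |
| 0.3 | 13.6% |
| 0.5 | 12.6% |
| 0.6 | 11.8% |
| 0.7 | 10.9% |
| 0.8 | 9.8% |

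The baseline comparison is not counted. Section 2.5 places that assessment before randomisation, so it is not a test of the intervention.

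**4. What the remedies cost.** Take 80% power, equal arms of 192.5 and all 385 women analysed; all three are assumptions. The detectable standardised difference is d = (z for alpha + 0.842) × √(2/192.5).
- One test at 5%: (1.960 + 0.842) × 0.1019 = 0.286.
- Bonferroni over three (0.05/3 = 0.0167): (2.394 + 0.842) × 0.1019 = 0.330.
- Sample size needed to offset the Bonferroni split: [(2.394 + 0.842)/(1.960 + 0.842)]² = 1.33 times as many women.

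**The case against.** The strongest reply is that model, contrast and testing order normally belong in a statistical analysis plan, which is not shown, and that a journal article condenses its protocol. This is right as far as it goes: the absence of a named model or an alpha split is not the point here. What stands is that the article itself fixes the primary outcome, and fixes it as three unranked times. An analysis plan that later chose one would be narrowing that outcome, not filling a gap.

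A reader might infer that the design carries a false-positive risk of about 12%. The documents do not support that as a flat statement. Section 2.9 describes one primary analysis and includes the baseline, which fits a single repeated-measures analysis at least as well as three separate tests. One overall test, or a requirement that all three times succeed, would not inflate the error. The correlation is assumed as well.

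A reader might also infer that the first score is usually antenatal. No distribution of gestational age at entry is given, and the share moves from 81% to 50% as the assumed window narrows. Section 3.4 expects some women to stall, which would delay the score in the intervention arm. The control arm's score is set at six weeks, so that argument does not reach it.

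Finally, two of the three times are postpartum and do address the objective, and nothing commits the authors to reporting an antenatal difference as postpartum prevention. That is fair. The definition nevertheless permits it.

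**Conclusion.** The point holds in a limited form. The stated primary outcome does not match the stated objective, because one of its three equal-ranking times precedes birth for every woman who starts before about week 34 and finishes on schedule. The week-34 limit rests on a 40-week term. The 50% to 81% share rests on assumed even entry.

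The false-positive risk is conditional: about 10% to 14% if three separate two-sided 5% tests are run and any one counts, for correlations from 0.8 to 0. The documents state neither that rule nor one that would keep the risk at 5%. Adjusting the significance level would deal with this part only; the antenatal score would still be a primary result.

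**What to change.** By a dated amendment, made without sight of outcome data by arm, name one postpartum PHQ-9 comparison as the sole primary outcome at two-sided 5%. Candidates are the difference at 3 months after delivery, or one joint 3-and-6-month contrast from a repeated-measures model. The documents do not favour one over the other, or over 6 months alone; the essential step is to commit to one. Make any remaining postpartum time, and then end of intervention, ordered secondary outcomes. Apply the same ordering to the GAD-7. Bring sections 2.3.1 and 2.9 and the Abstract into line. The same edit should settle the follow-up anchor, which section 2.1 counts from the due date and section 2.3.1 from delivery.

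No extra women or visits are needed, but this is more than an edit of wording: section 2.1 puts recruitment between 2020 and 2022, so the change may fall during the trial and needs a recorded reason. A success seen only at a non-primary time could no longer be called the primary result. A reader might suppose that naming one time costs no power. That is true against a single 5% test, but the chance of claiming success is lower than under an uncorrected any-of-three rule. Keeping all three times with a Bonferroni split would cost more (d = 0.330 instead of 0.286, or 1.33 times the sample) and would leave the mismatch with the objective in place.
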